## Abstract

**Abstract:**

**Background:**

Risk screening for pre-eclampsia relies on accurate gestational age assessment, but routine access to ultrasound-based gestational dating remains challenging in many low- and middle-income countries. As part of the formative work for the ‘Preventing pre-eclampsia: Evaluating AspiRin Low-dose regimens following risk Screening’ (PEARLS) platform, we aim to validate and implement an artificial intelligence (AI)-based algorithm for estimation of gestational age, using blind sweeps done with a handheld ultrasound device. This study protocol outlines the accuracy cohort for AI-based gestational age estimation in participating facilities in Ghana, Kenya and South Africa.

**Methods and analysis:**

This multicountry prospective cohort study will recruit 969 pregnant women at 13 health facilities across Kenya, Ghana and South Africa. The eligible population is pregnant women presenting for antenatal visits from 11^+0^ to 13^+6^ weeks’ gestation. Eligible women will have a gestational age assessment by a trained sonographer using fetal biometry (reference standard), followed by gestational age estimation conducted by a trained midwife using the AI-based Intelligent Ultrasound ScanNav FetalCheck system (experimental). Both conventional and AI-based gestational age scans will be conducted with the General Electric VScan Air platform. Women will return for a second visit between 14^+0^ and 27^+6^ weeks’ gestation (week of visit is randomly selected) for an assessment with both conventional and AI-based ultrasound. The primary objective is to determine the accuracy and precision of gestational age estimation using an AI ultrasound system in first and second trimesters, as compared with gestational age estimation using crown-rump length measurement by conventional ultrasound in first trimester (11^+0^ to 13^+6^ weeks’).

**Ethics and dissemination:**

This study has received or sought ethics approval from the following entities: Australia: University of Melbourne, Office of Research Ethics and Integrity (Reference Number: 2024–28489-49438-3) and the Alfred Hospital Ethics Committee (Reference: Project 727/23); Ghana: Ghana Health Service Ethics Review Committee (GHS-ERC Number 002/01/24); Kenya: Kenyatta National Hospital, University of Nairobi ERC (Ref: KNH-ERC/01/MISC/20); South Africa: University of Cape Town, Faculty of Health Science, Human Research Ethics Committee (HREC Ref: 138/2024). Key findings will be disseminated to research teams to inform future scale-up of AI-based pregnancy dating and pre-eclampsia risk screening. Findings from this pilot work will be published in peer-reviewed open-access journals, conferences and meetings to maximise reach of our findings.

STRENGTHS AND LIMITATIONS OF THIS STUDYThis study uses a large, multicountry prospective cohort across 13 diverse health facilities in Ghana, Kenya and South Africa, which supports generalisability of findings across varied health system contexts.The protocol includes standardised training for sonographers and midwives, as well as the use of consistent ultrasound platforms, which strengthens internal validity and reduces measurement variability.First trimester crown-rump length measurements by trained sonographers serve as the reference standard, allowing robust assessment of accuracy and precision of the artificial intelligence-based gestational age estimates.The use of blind ultrasound sweeps collected by midwives reflects real-world conditions and enhances the applicability of results to routine antenatal care, particularly in settings with limited specialist availability.Interoperatory variability in both conventional ultrasound scanning and blind-sweep technique may still occur despite standardised training, which could influence the quality and consistency of image data, but also reflects real-world contexts.

## Introduction

 Pre-eclampsia remains a leading cause of maternal morbidity and mortality globally, causing an estimated 46 000 maternal deaths annually, over 90% of which occur in low- and middle-income countries (LMICs).^1^ Pre-eclampsia is also a major cause of maternal and neonatal morbidity, including maternal kidney and liver dysfunction, stroke and seizures and fetal growth restriction, stillbirth and preterm birth.^2^ Preventive measures, such as identifying women at high risk of developing pre-eclampsia and offering them daily aspirin exist, but are poorly implemented. Many of these deaths could be prevented by implementing systematic risk screening of all women and risk stratification-based care pathways and preventive measures. The World Health Organization (WHO) recommends that all women who are at moderate or high risk of developing pre-eclampsia should be offered low-dose aspirin for prevention, ideally prior to 20 weeks’ gestation.^3^ Effective implementation of this strategy requires accurate and scalable approaches to risk screening during early pregnancy.

The Preventing pre-eclampsia: Evaluating AspiRin Low-dose regimens following risk Screening (PEARLS) was established to evaluate the performance of a modified Fetal Medicine Foundation (FMF) risk prediction approach in LMIC settings. Pregnant women were recruited from antenatal care facilities in Ghana, Kenya, South Africa and India to validate a ‘restricted-variable’ FMF model and assess its feasibility for implementation in routine care.^4
5^

The FMF tool uses a Bayesian model combining information on demographic and clinical history-based risk factors, gestational age, as well as mean arterial pressure, Uterine Artery Doppler Pulsatility Index (UTPI), placental growth factor levels and/or pregnancy-associated placental protein A levels.^6
7^ In European settings using a risk threshold of ≥1 in 100, the FMF tool has a detection rate (sensitivity) of 80.7% for preterm pre-eclampsia (<37 weeks’ gestational age), with a false positive rate of 14.1%.^7^ Even in the absence of the UTPI and blood-based biomarkers, the detection rate is 66.7%, with a false positive rate of 17.9%.^7^ The FMF tool has been validated in Western European and Asian populations,^8^ and has been assessed in a single tertiary facility in India.^9^ However, the FMF tool has not been validated or implemented at scale in African or South Asian countries. Certain variables within the FMF tool are not routinely available in antenatal care in many LMICs, particularly serum biomarkers, uterine artery Doppler and reliable gestational age estimation using ultrasound. Accurate dating is critical to the provision of risk screening for pre-eclampsia using the FMF-based approach, and in turn implementing a strategy of pre-eclampsia prevention using low-dose aspirin.

### Ultrasound for gestational age assessment: essential but out of reach in many LMICs

WHO recommends that all pregnant women should be offered an antenatal ultrasound before 24 weeks gestation, stating that ultrasound-based estimation of gestational age and detection of fetal anomalies and multiple pregnancies, improve women’s antenatal care and timing of birth and may improve women’s pregnancy experience and pregnancy outcome.^10^ It also helps ensure appropriate use of gestational age-specific interventions, such as initiating low-dose aspirin for women at risk of pre-eclampsia prior to 20 weeks’ gestation.^3^ Implementation of antenatal ultrasound for all pregnant women relies on availability of ultrasound devices facilities in which to conduct scans in a safe, private space and staff who are adequately trained and supported to use and interpret ultrasound images. National standards and training requirements for ultrasound use and associated care following ultrasound screening vary across countries, and influence routine ultrasound implementation.^11^ Many women, particularly those in limited-resource settings or who access antenatal care at primary health centres, lack access to routine antenatal ultrasound.^12
13^ In tackling this healthcare gap, the development of smaller, portable and handheld ultrasound devices is rapidly expanding, which could help improve women’s access to antenatal ultrasound in these settings.^14^

The application of artificial intelligence (AI) models and deep learning techniques have generated new approaches to interpreting medical imaging, including antenatal ultrasound.^15–17^ Algorithms that are trained on a database of high-quality, labelled ultrasound images (where the gold standard gestational age is known) can learn to estimate gestational age accurately, without the need for human expert measurement and interpretation of fetal biometry. Typically, such an AI model would ‘read’ images obtained through blind abdominal sweeps with a point-of-care ultrasound device. These sweeps can be performed by a person with minimal (rather than expert) training. Intelligent ultrasound (IU, now part of GE HealthCare) is one of several companies that have developed an AI-based tool, called the ScanNav FetalCheck system. This system estimates gestational age from ultrasound images obtained via the General Electric (GE) VScan Air handheld ultrasound device.

### Rationale for a prospective cohort study on AI-based gestational age estimation in sub-Saharan Africa

Implementing an AI-based ultrasound will introduce new challenges for health services. While some women in Ghana, Kenya and South Africa will have had a conventional ultrasound prior to being screened for eligibility to the study, approximately just under a half to three-quarters of women will not, based on PEARLS site investigators’ estimates. Potential benefits of this AI-based ultrasound system for PEARLS include:

AI-based ultrasound can be performed by a health worker with minimal (rather than specialist) training, so gestational age estimation can be scaled up more quickly and easily.The gestational age estimate is generated by the software immediately and does not require expert review or interpretation.The IU ScanNav FetalCheck system uses GE’s handheld, point-of-care ultrasound device. The latter is commercially available, and has previously received regulatory approval in Ghana, Kenya, South Africa and many other countries.The hand-held, point of care ultrasound device allows easy transit between multiple sites, and the smaller size means it can be used in multipurpose clinical areas.

The algorithm underpinning this functionality has been trained on a retrospective dataset of over 2 million antenatal ultrasound images from over 75 000 pregnant women, obtained from centres in Australia, India and the UK.^18^ It has been validated in silico (retrospective computer-based validation) using a separate retrospective validation dataset of over 700 patients, also from Australia, India and the UK. These studies showed the AI-based algorithm showed a mean absolute error of 1.7 days between 14 and 18 weeks gestational age and 2.8 days between 18 and 24 weeks, outperforming traditional fetal biometry.^18^

However, the IU ScanNav FetalCheck system has not been evaluated in a prospective study in real-world clinical settings for first or second trimester gestational age estimation or in African pregnancies and settings. That is, whether this system has similar (equivalent) accuracy to current standard-of-care using conventional ultrasound for pregnant women in PEARLS settings is currently unknown. If the system is shown to be at least equivalent to the current standard of care, the gestational age estimate it generates can be considered reliable for the purposes of informing FMF-based risk screening and aspirin implementation. In a mixed-methods formative research study, we will also identify challenges and the feasibility of implementing AI-based gestational age estimation using hand-held ultrasound (protocol published separately).^5^

#### Primary aim

This study aims to assess the accuracy and precision of the IU ScanNav FetalCheck system (‘IU system’) compared with conventional ultrasound for gestational age estimation, in pregnant women in Ghana, Kenya and South Africa.

#### Primary objectives

1. Determine accuracy and precision of gestational age estimation by IU system in first trimester (11^+0^ to 13^+6^ weeks) as compared with gestational age estimation using crown-rump length (CRL) measurement by conventional ultrasound in first trimester (11^+0^ to 13^+6^ weeks).

2. Determine accuracy and precision of gestational age estimation by IU system in second trimester (14^+0^ to 27^+6^ weeks) as compared with gestational age estimation using CRL measurement by conventional ultrasound in first trimester (11^+0^ to 13^+6^ weeks).

#### Secondary objectives

3. Determine accuracy and precision of gestational age estimation by IU system in second trimester (14^+0^ to 27^+6^ weeks) as compared with fetal biometry by conventional ultrasound in second trimester (14^+0^ to 27^+6^ weeks).

4. Determine the accuracy of identifying women at <20 weeks’ gestation by conventional ultrasound using second trimester fetal biometry, as compared with IU system in second trimester.

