#### Gestational age estimation

##### Conventional ultrasound estimation (standard care)

At each study visit (first and second trimesters), study sonographers will use conventional ultrasound to assess gestational age as outlined in box 1.

Box 1Fetal biometry measurement practice for gestational age estimationWomen in first trimester:Abdominal ultrasound will be used to obtain three crown-rump length (CRL) measurements. The best measurement will be selected, and gestational age will be calculated using INTERGROWTH-21st charts.^23^ The best CRL measurement by clinical judgement and associated image will be entered into Research Electronic Data Capture (REDCap).Women in second trimester:At the second trimester ultrasound, biparietal diameter, head circumference (HC), abdominal circumference and femur length are each measured three times. The best measurement by clinical judgement of each (and associated image) will be entered into REDCap.Gestational age will be estimated using the INTERGROWTH-21 curves based on HC value (mm).^24^

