#### Analysis

Baseline characteristics of study participants will be described using means and SDs for normally distributed variables, medians and 25th and 75th percentiles for non-normally distributed variables and frequencies and percentages for binary and categorical variables.

Analysis for objectives 1, 2 and 3 will estimate (with 95% CIs) the mean difference and 95% limits of agreement between the gestational age estimates by IU and CRL (objective 1), ‘extrapolated CRL’ (objective 2) or fetal biometry (objective 3). Extrapolated CRL is the CRL-estimated gestational age plus the time difference (in days) between an individual’s first (Visit 1) and second trimester (Visit 2) measurement dates. The mean difference and 95% limits of agreement will be displayed with their 95% CIs within a Bland-Altman style plot of the mean differences (y-axis) and average estimated gestational age (x-axis). In addition, fixed and proportional bias between gestational age estimates obtained using conventional ultrasound and the IU device will be evaluated using reduced major axis regression (RMAR).^24^ RMAR provides the slope and intercept of the regression line. A slope different from one indicates proportional bias, meaning that the magnitude of the difference between gestational age measured by conventional ultrasound and IU device varies with the magnitude of the conventional ultrasound measurements. If no proportional bias is present, an intercept different from 0 indicates fixed bias, meaning the difference between the two gestational age measurement methods remains consistent across the range of conventional ultrasound gestational age estimates.

Analysis of objective 4 will estimate (with 95% CIs) the measures of diagnostic performance (specifically the detection rate and the false positive rate) of the IU gestational age estimation approach for classifying individuals as less than 20 weeks’ gestation, compared with conventional ultrasound fetal biometry, both measured at the second trimester, as binomial proportions. The complete data analysis plan is described in online supplemental appendix B.

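### Objective 4 reverses test and comparator relative to its own analysis, and its detection and false positive rates measure agreement with second-trimester HC dating rather than accuracy against the protocol's CRL reference standard

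*Protocol article*

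**What the plan says.** Under Secondary objectives, objective 4 is about the "accuracy of identifying women at <20 weeks’ gestation by conventional ultrasound using second trimester fetal biometry, as compared with IU system", both taken at the second visit. Read literally, conventional second-trimester biometry is being assessed and IU is the comparator.

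The Analysis section describes objective 4 as detection and false positive rates, with 95% CIs, "of the IU gestational age estimation approach for classifying individuals as less than 20 weeks’ gestation, compared with conventional ultrasound fetal biometry". There IU is the test and biometry is the reference.

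The second-trimester conventional estimate rests on HC alone (Box 1 under Conventional ultrasound estimation; also Participant flow and follow-up).

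The strengths and limitations box states: "First trimester crown-rump length measurements by trained sonographers serve as the reference standard". The Analysis section defines an extrapolated CRL age at Visit 2 (CRL age plus the days elapsed since Visit 1) and uses it for objective 2. The objective 4 analysis does not mention it.

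**The concern.** There are two linked problems.

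First, a detection rate is conditional on being positive by the reference, so the objective must say which method is the reference. The objective and its analysis give opposite answers.

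Second, whichever way round it is read, a second-trimester measurement with error of its own stands in for truth. When IU and HC disagree near 20 weeks, the two-by-two table cannot show which was wrong. Independent HC error makes IU look worse than it is. Error shared by the two methods, for example from a fetus large or small for its age, counts as agreement and makes IU look better.

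The Introduction ties the start of aspirin to the period before 20 weeks, and objective 4 is the only objective that reports classification at that threshold. Its rates are likely to be quoted as the accuracy of IU for that purpose.

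**Working it through.** **Roles, side by side**

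| Place | Under test | Compared with |
|---|---|---|
| Primary aim | IU | conventional ultrasound |
| Objectives 1, 2 | IU | first-trimester CRL |
| Objective 3 | IU | second-trimester biometry |
| Objective 4, as worded | second-trimester biometry | IU |
| Objective 4, as analysed | IU | second-trimester biometry |

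The wording of objective 4 is the only row with IU as comparator.

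**The plan's own figures.** None is given for objective 4. The sample size, set on limits of agreement, reproduces closely. With Var(limit) = s²(1 + 1.96²/2)/n and a half-width of 10% of 1.96s, n = 2.92/0.01 = 292, against 290 stated. Then 290/0.9 = 322.2, rounded up to 323, and 3 × 323 = 969. This point does not change it.

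**Inputs from the protocol.** Visit 2 is at a random time from 14+0 to 27+6 weeks. The cut-off is 20+0 weeks (140 days). The in silico mean absolute error of IU at 18 to 24 weeks is 2.8 days. If errors are normal, SD = 2.8 × √(π/2) = 3.5 days.

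**Assumptions not in the protocol.** Visit timing is uniform on 98 to 196 days, so 42/98 = 43% of women are truly below 20 weeks. HC error SD is 4 to 7 days and extrapolated CRL error SD is 2 to 3 days. CRL error is independent of IU error. Errors are unbiased unless stated.

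**Model.** At true age t, a method with bias b and SD s reads below 140 days with probability Φ((140 − t − b)/s). Detection = P(IU < 140 and reference < 140)/P(reference < 140). False positive rate (FPR) = P(IU < 140 and reference ≥ 140)/P(reference ≥ 140). Both are averaged over t, with bivariate normal errors where correlated. IU SD is 3.5 throughout.

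| IU scored against | Detection | FPR |
|---|---|---|
| error-free truth | 96.7% | 2.5% |
| extrapolated CRL, SD 2 | 96.2% | 2.9% |
| extrapolated CRL, SD 3 | 95.6% | 3.3% |
| HC, SD 4, independent | 94.9% | 3.8% |
| HC, SD 5, independent | 94.2% | 4.4% |
| HC, SD 7, independent | 92.6% | 5.6% |
| HC, SD 5, correlation 0.5 | 95.8% | 3.2% |
| HC, SD 3.5, correlation 0.8 | 97.9% | 1.6% |

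An error-free IU scored against unbiased HC of SD 5 would read 95.2%/3.6%.

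**Swapping the roles.** With both methods unbiased and uniform timing, each calls the same share of women below 20 weeks. The two discordant cells are then equal, and so are the rates in either direction: 94.2%/4.4% both ways at HC SD 5. An HC bias of −3 days moves the HC-positive share to 45/98 and breaks the symmetry. IU against HC then reads 90.6%/2.3%, and HC against IU reads 97.1%/7.5%.

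**Sampling error for scale.** With 290 women in a country, about 124 are below 20 weeks and 166 are not. At 94.2%/4.4% the 95% half-widths are about 4.1 and 3.1 points. Pooled over 870 women they are about 2.4 and 1.8 points.

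**The case against.** The Analysis section fixes the test, the comparator and the measures, and it agrees with the primary aim and objectives 1 to 3. The wording of objective 4 can therefore be read as a slip of one line. This stands: the analysis is not left open, and the repair is editorial.

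Comparison with second-trimester biometry is also a stated question. The rationale asks whether IU is equivalent to the current standard of care, and objective 3 makes the same comparison on the continuous scale. Objective 2 already sets IU against extrapolated CRL. This stands too: the HC comparison should be kept. What it does not justify is presenting its result as accuracy or diagnostic performance.

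A reader might infer that the reversal in itself yields two different sets of results. The documents do not support that. The directions differ materially only under an HC bias, and the protocol gives none.

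A reader might also quote the 1.7-fold rise in FPR (4.4% against 2.5%). That sets HC against error-free truth, which no reference here supplies. Against extrapolated CRL the ratio is about 1.3 to 1.5 (4.35/3.28 to 4.35/2.87) for HC SD 5 with independent errors. At correlation 0.5 it disappears.

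It would also be too strong to say that the CRL reference exists for every woman: images that fail quality assessment are not used in the final analysis. Finally, the full analysis plan is in supplemental appendix B, which is not shown, so a CRL-based classification may already be planned there.

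**Conclusion.** Both textual facts are established: the objective and its analysis assign opposite roles, and the objective 4 rates are referred to HC dating although the protocol names CRL as its reference standard and already extrapolates it to Visit 2. The rates therefore describe agreement with HC-based classification.

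The likely distortion is modest and its sign is not known in advance. For IU SD 3.5 days and independent errors, detection against HC is lower than against extrapolated CRL by 95.6 − 94.9 = 0.7 to 96.2 − 92.6 = 3.6 points across the assumed SDs. With correlated errors the difference can vanish or favour IU. These figures rest on normal, unbiased errors and on HC and CRL SDs that the protocol does not give. The distortion is of the same order as the sampling error in one country, but a larger sample would not remove it.

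Severity is moderate. A reader might take this as undermining the study's accuracy claims generally. It does not: objective 4 is secondary, and objectives 1 and 2, the sample size and the data collection are unaffected.

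**What to change.** 1. Reword objective 4 so that IU is the index test, in line with the Analysis section.
2. For classification as below 20+0 weeks, report detection and false positive rates of IU, and separately of second-trimester HC, each against extrapolated CRL in women with a usable CRL image. Add the paired IU minus HC difference in each rate, with a McNemar-type 95% CI. This answers whether IU classifies as well as current practice.
3. Keep the IU-by-HC cross-table as the standard-of-care comparison, labelled agreement.
4. If appendix B already contains the CRL-based classification, bring the article's wording into line with it.

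The cost is a few lines of text and a small extra analysis. All measurements are already collected, and no change to sample size is needed.
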